Six months after baseline, the care staff for the control group will receive the same training on how to implement the MAKS-s intervention as the care staff for the intervention group. After the 6-month intervention phase, the intervention and the control groups will be free to decide whether to continue or to begin the MAKS-s intervention, respectively.

The observation period will last 12 months, with a total of four measurement points (baseline, 2, 6, and 12-month follow ups).

The data will be collected by means of nursing home documents, psychometric tests, and external rating scales (see the “Measures” section). All procedures were approved by the Friedrich-Alexander University Erlangen-Nürnberg Ethics Committee. The external GKV Spitzenverband (the institution providing funding) is being regularly informed of the progress of the study and the milestones that have been achieved as set forth in the trial application. The SPIRIT participant timeline is presented in Table 1. When important protocol modifications are required, we will inform the Ethics Committee, the funding institution, the nursing homes, and the platform for the trial registry. The trial registration data are displayed in Table 2.

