### Sample size estimation

#### Primary target group

A power analysis was computed on the basis of the authors’ previous experience with the pilot study MAKS-s ([name]: Modification and implementation of the MAKS-aktiv! therapy with severrly demented people: a pilot experiment, unpublished master´s thesis, Friedrich-Alexander University Erlangen-Nürnberg). For this purpose, the effects of the subscales “mood”, “disturbing behaviour”, and “social behaviour” of the NOSGER (“Nurses’ Observation Scale for Geriatric Patients”) [27] were pooled. The result was an effect size of Cohen’s *d* = 0.52. The beta-error was set to four times the size of the alpha error (α = .05), as proposed by Cohen [28]. This resulted in a power of .80.

Under these conditions, an evaluation sample of 114 individuals (57 per group, 6 per nursing-home) was deemed necessary. On the basis of the previous MAKS study [10], we expect a drop-out rate (mainly caused by death or being bed-ridden) of 20% across 6 months. This means a total of 144 people with severe dementia has to be included in the study. To achieve this goal, only nursing homes with at least 40 residents are being included in the project. This could be deduced from the following considerations:
In nursing homes in Germany, 38.8% of residents suffer from severe dementia [1]. This means 15 out of 40 individuals.In the “MAKS aktiv” study, the rate of bedridden and/or blind/deaf residents was 26% [10]. In the group of severe dementia cases, this rate was 40%. This left 9 of the 15 people with severe dementia suitable for intervention.It can be assumed that at least 70% of the participants will be willing to participate after the legal representatives have been informed [10]. Thus, 6 of the 9 suitable PWSDs can be included in the study.

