### Analysis

#### Data analysis

In order to revise the quality of randomisation, the baseline data from the intervention and the control groups will be compared for statistically significant differences.

Descriptive statistics will be reported on all variables from the primary target group (PWSDs), such as age, sex, level of care, or Charlson Index, and from the secondary target group (formal caregivers), such as age, sex, or profession.

Hypotheses 1 to 3 will be tested by applying multiple regression analyses. To ensure the robustness of the results, both data analytic strategies “intention to treat” and “per protocol” will be applied. “Intention to treat” evaluations are carried out with all cases are still alive at the end of the intervention period.

Differences in days spent unable to work among the formal caregivers in the intervention group facilities compared with those in the control group (Hypothesis 4) will be tested for significance using the *t*-test for independent groups.

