#### Economic evaluation

To show the effects on the cost to the health care system, we will conduct an economic analysis of the days spent unable to work for the nursing and care staff members who are primarily involved in the care of the PWSDs.

Missing data will be imputed by using the expectation maximum (EM) algorithm. The data analysis will be performed with the “IBM SPSS Statistics 24” software. All analyses will be conducted under the supervision of the cooperation partner IMBE.

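### The set labelled intention to treat contains only residents alive at the end of the 6-month intervention, so it is a survivors-only set and should be renamed and supplemented

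*Protocol article*

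**What the plan says.** The Data analysis section states that "Hypotheses 1 to 3 will be tested by applying multiple regression analyses". It applies an intention-to-treat and a per-protocol strategy to these tests, with the stated purpose: "To ensure the robustness of the results, both data analytic strategies". Neither is named as primary. The only definition given for either set is that intention-to-treat "evaluations are carried out with all cases are still alive at the end of the intervention period".

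Three other places bear on this:

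- **Sample size estimation, Primary target group:** "we expect a drop-out rate (mainly caused by death or being bed-ridden) of 20% across 6 months". The split between the two causes is not given.
- **Study design and setting:** a 12-month observation period "with a total of four measurement points (baseline, 2, 6, and 12-month follow ups").
- **Economic evaluation, last paragraph:** "Missing data will be imputed by using the expectation maximum (EM) algorithm". Nothing there says that imputation extends to residents who have died.

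Under Other measures, the monitoring form records deaths during the intervention period.

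**The concern.** Randomisation makes the two groups of homes comparable in the residents they contain at the start. Whether a resident is alive six months later is settled afterwards and could in principle depend on the arm. A set chosen on that condition is no longer protected by the randomisation, whatever it is called.

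The label matters because a reader of the results will take intention to treat to mean that every randomised resident counted. Under this definition that would be untrue. The second strategy offers no safeguard: the article nowhere says that the per-protocol set brings back residents who died, and such a set is normally the narrower of the two. Giving both analyses therefore says nothing about robustness to this selection.

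Death is not a remote possibility here. The sample size section names it as a main cause of loss, and the article's description of the comorbidity index quotes 1-year mortality from 12% at the lowest score to 85% at the highest.

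The definition also drops a resident who dies between months 2 and 6 altogether, including any outcome score taken at month 2.

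**Working it through.** **Step 1. The plan's own figures.** Inputs from Sample size estimation: d = 0.52, α = 0.05, power 0.80, 57 per group (114 in total), 20% loss, 144 enrolled.

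- A two-sided two-sample comparison needs 59 per arm. At 57 per arm the power is 0.793 (normal approximation) or 0.786 (t-test). One-sided testing would need 46 per arm, so the figures fit a two-sided test.
- Inflation for loss: 114 / 0.80 = 142.5, rounded up to 143. The design gives 24 homes × 6 = 144.

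The plan's figures reproduce closely. The point here does not depend on them.

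**Step 2. How many residents the definition removes.** Expected loss is 144 × 0.20 = 28.8, about 29. Only deaths leave the set. A resident who becomes bedridden is alive and stays in, with imputation where scores are missing. As the split is not stated:

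- no deaths among the losses: 0 removed, 144 remain;
- all losses are deaths: about 29 removed, about 115 remain.

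**Step 3. Bias of a survivors-only contrast.** Let δ be the amount, in SD, by which residents who die would score worse than survivors, taken as equal in both arms. Let p_I and p_C be 6-month mortality in the two arms. Each arm's survivor mean is better than its full mean by p × δ, so

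size of bias = δ × |p_I − p_C|,

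and the arm with more deaths is flattered. The documents give neither δ nor the mortality gap, so the inputs below are assumptions.

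| δ (SD) | Mortality gap | Bias (SD) | Share of d = 0.52 |
|---|---|---|---|
| 0.5 | 0.05 | 0.025 | 5% |
| 0.8 | 0.10 | 0.080 | 15% |
| any | 0 | 0 | 0% |

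**Step 4. Check by simulation, all inputs assumed.** The true effect is set to zero. Frailty drives both death and outcome, with a frailty–outcome correlation of 0.3 to 0.7 and a correlation of 0.7 between frailty and the liability to die. The bias is shown in absolute value.

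| Mortality in the two arms | Bias (SD) |
|---|---|
| 20% and 20% | 0.000 to 0.003 |
| 20% and 15% | 0.016 to 0.038 |
| 20% and 10% | 0.036 to 0.077 |

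With 25% against 15%, exchanging the arms reverses the sign. The range agrees with Step 3.

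**Step 5. Scale.** Ignoring clustering, the standard error of a standardised difference at 57 per arm is about √(2/57) = 0.187. The bias in Step 3 is 0.025 / 0.187 = 13% to 0.080 / 0.187 = 43% of one standard error.

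**The case against.** The strongest defence is that NPI-NH and QUALIDEM scores do not exist after death. A comparison among survivors, or one of scores while alive, can be a legitimate target. That stands, but such a target has to be named and justified, and the article instead gives it the label of a different one.

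A second defence is that nothing in the article suggests MAKS-s affects mortality; the Implementation section expects no serious adverse events. If mortality and the kind of resident who dies are unrelated to arm, the expected bias is about zero, and a chance imbalance in deaths adds noise rather than systematic error. This also stands and limits the severity.

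A reader might draw four stronger conclusions that the documents do not support:

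- **That the primary analysis is survivors-only.** Neither strategy is named as primary. What can be said is that the set called intention to treat excludes deaths.
- **That 29 residents will be lost to the definition.** This is a ceiling that requires every loss to be a death, whereas the article also names becoming bedridden.
- **That month-2 outcome scores are certainly thrown away.** The article lists a 2-month measurement point, but the instrument schedule is in Table 1, which is not reproduced in the text at hand. That both primary outcomes are scored then is an assumption.
- **That the per-protocol analysis is biased in favour of MAKS-s.** The article does not define that set, so no such bias can be derived or sized.

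**Conclusion.** The definition is wrong as written. It is an explicit rule, so it cannot be excused as detail left to a fuller document, and neither the imputation statement nor any other text restores residents who died. In practice it bears on Hypotheses 1 and 2, which concern residents; Hypothesis 3 concerns staff.

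The consequence is moderate. The certain part is the mislabelling and the absence of any described analysis of all randomised residents. The bias is conditional: its size rests wholly on the assumed mortality and outcome gaps, and its direction is unknown. A reader might infer that the trial's effect estimate will be materially distorted; the figures do not show that. This is a point that should be fixed, and it does not by itself invalidate the comparison.

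**What to change.** Before outcomes are examined by arm:

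1. Define the intention-to-treat set as all consented residents of randomised homes, analysed according to the home's allocation.
2. Include the available post-baseline scores of residents who later die, for example in a mixed model with the 2- and 6-month scores, provided the outcomes are scored at month 2.
3. State how death is handled. A mixed model alone does not settle this: by treating scores after death as missing at random, its month-6 contrast describes residents as if nobody had died. Candidates are a while-alive target, a composite in which death ranks worst, or a survivor-average effect. The choice belongs to the trial team and needs a reason.
4. Report deaths by arm.
5. Keep the present analysis as a sensitivity analysis under the name survivors-only.
6. Declare intention to treat primary and per protocol supportive.

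The cost is revised wording, slightly more analysis work and the need to commit to a treatment of death. Deaths are already on the monitoring form. No new data collection is needed if the primary outcomes are scored at month 2; if they are not, step 2 adds nothing for residents who die before month 6, and the other steps still apply.

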## Methods/design

### Aims and hypotheses

The main aim of the MAKS-s study, which began in July 2019, is to find out whether a non-pharmacological intervention adapted to the special needs of PWSDs can reduce the BPSD of this target group (primary target group) and consequently improve their Qol. In addition, we expect that the intervention will enable the maintenance of basal activities of daily living (ADLs). There is also the possibility that this improvement will provide some relief for the formal caregivers (secondary target group), which will be shown in a reduction in the number of days spent unable to work.

Research hypotheses:

Based on the primary outcome:
I.By participating in MAKS-s, the BPSD and Qol of PWSDswill be significantly better in the intervention group than in the control group.

Based on the secondary outcome:
II.By participating in MAKS-s, the everyday practical skills of PWSDswill be significantly better in the intervention group than in the control group.III.In the care facilities in which MAKS-s is conducted, the dementia-related stress experience of the nursing and care staff (secondary target group) involved in the care of the participants will be significantly better in comparison with the nursing and care staff in the control facilities.IV.The assumed positive trend described in Hypothesis 3 will lead to a relevant reduction in the number of days spent unable to work for this group of individuals.

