### Study design and setting

A two-armed cluster-randomised, controlled, multicentre, prospective longitudinal study with a waitlist control group design will be conducted to test the abovementioned hypotheses.

The nursing homes are located in five areas (German federal state): Bavaria, Baden-Württemberg, Thuringia, Rhineland-Palatinate, and Saarland. All nursing homes (clusters) participating in the study will be randomly assigned to the intervention or control groups at baseline (through random selection) by our cooperation partner “Institut für Medizininformatik, Biometrie und Epidemiologie (IMBE)” at the Friedrich-Alexander University Erlangen-Nürnberg. The clusters will be allocated by applying a tree-step stratification process by using “protective versus non-protective ward”, “area”, and “nursing home size” in decreasing order to balance the structural parameters.

The contact people in each nursing home are trained by the study headquarters with respect to the study protocol, instruments, and screening procedure before randomisation. Informed consent from the legal representatives of the PWSDs and the nursing staff (i.e., trained nurses) and care staff (i.e., staff with no medical training) will also be obtained before randomisation. Nursing homes will be informed about their group assignment in written form by the study headquarters. In addition, the nursing homes in the intervention group will receive further training on the implementation of the MAKS-s intervention. This treatment will be performed through the 6-month intervention phase. The nursing homes in the control group will not carry out any specific treatment but will continue providing “care as usual”.

Because we are investigating a non-pharmacological intervention, not everybody participating in the study can be blinded. Due to the severity of dementia, we can assume that the PWSDs will be blind to the conditions of the study. The therapists performing the MAKS-s intervention cannot be blinded. The raters (nursing staff) will be “semi-blinded”. They will know about the group assignment but will have no knowledge of the intervention. The testers, who are trained students from the study headquarters, who will conduct the tests, will be completely blinded.

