#### Secondary target group

The sample size of the secondary target group could not be deduced empirically. The number of members from the secondary target group will depend on the structural conditions of the nursing homes. In every nursing home, there must be a minimum of 6 individuals (MAKS-s therapists and other nursing staff) who meet the criteria for inclusion in the study.

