### Recruitment strategies

Nursing homes from the postulated size in the recruitment areas are identified by means of their websites. Information material is sent to these nursing homes by post. Two weeks later, all the facilities that have been contacted are called by telephone and asked whether they are willing to participate. Cooperation contracts are signed with the nursing homes that are interested in participating in the study. After at least 24 nursing homes have signed a cooperation contract, recruitment will be completed.

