##### Secondary target group

*Professional Care Team Burden (PCTB) Scale* [43]*.* The PCTB is a self-rating scale for assessing the subjective burden of the professional care staff in nursing homes and other caregiving facilities. The measure contains 10 items divided into 3 subscales (structural burden, objective burden, subjective burden). The items are rated on a five-point scale ranging from strongly disagree to strongly agree. The total score ranges from 0 to 40 points, with lower values indicating higher burden.

The convergent validity was demonstrated by computing the correlation with the Perceived Stress Scale (PSS), indicating moderate to high validity [43]. Cronbach’s alpha for the complete scale was .79.

*Days spent unable to work*. The number of days spent unable to work by the nursing and care staff who are most involved in the care of the participating PWSDs will be recorded by the head of the nursing home.

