### Strengths and limitations of the study design

The study design offers several strengths. The external validity of the study is high because of the naturalistic setting in nursing homes with nursing staff and the recruitment of nursing homes that are in different federal states of Germany, are in urban and rural regions, and are run by a wide variety of organisations (profit, non-profit, local authorities). Also the duration of the intervention of 6 months, the use of a manualised treatment, and the focus on two target groups (PWSDs and the nursing and care staff) have rarely been applied in international studies [15, 25, 49–51].

Another strength of the current study is the cluster randomisation. We decided to use cluster randomisation rather than randomisation because of the secondary target group. If we were to have a treatment group and a control group in the same nursing home, we could not observe any effect of the intervention on the formal caregivers because the caregivers may be responsible for both the people in the intervention group and the people in the control group. Furthermore, the intervention could not be withheld from any individual working in a nursing home without the possibility of “contaminating” the control group [52]. In order to avoid a systematic difference between the two arms of the study by chance, a three-step stratification process is being conducted to allocate the nursing homes. At the same time, to avoid a recruiting bias, recruitment will be completed before randomisation.

However, a limiting bias can occur. Because we are conducting a non-pharmacological intervention, the nurses who carry out the assessments (raters) are not completely blind to the conditions of the study because they know about the group assignment.

Because the study deals with PWSDs, due to the severe cognitive impairment of the participants, we could only use proxy-based ratings from an observer’s perspective. The perspective of the PWSDs themselves cannot be taken into account.

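### Hypothesis 4 (staff sick days) is given an independent-samples t-test with no allowance for nursing home, although homes are the randomised unit

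*Protocol article*

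**What the plan says.** Under Data analysis, the protocol article fixes the comparison for Hypothesis 4 as "Differences in days spent unable to work among the formal caregivers in the intervention group facilities compared with those in the control group", which "will be tested for significance using the *t*-test for independent groups". It mentions no home effect, cluster-robust standard error or aggregation to home level, either there or in the Economic evaluation section that follows.

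Other sections set the design:

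- Study design and setting: "All nursing homes (clusters) participating in the study will be randomly assigned to the intervention or control groups at baseline".
- Strengths and limitations of the study design gives the staff as the reason for clustering: "We decided to use cluster randomisation rather than randomisation because of the secondary target group".
- Recruitment strategies: "After at least 24 nursing homes have signed a cooperation contract, recruitment will be completed".
- Sample size estimation, Secondary target group: every home must have no fewer than 6 eligible staff, and the staff sample size was not derived empirically.
- Secondary outcome measures, Secondary target group: the days "will be recorded by the head of the nursing home".

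Table 2 lists days of incapacity for work among the key secondary outcomes.

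**The concern.** An independent-samples t-test assumes that every observation carries separate information. Staff of one home share an employer, residents and working conditions, and one person records their absences. Some within-home correlation is therefore plausible, although the article does not quantify it. Allocation is constant within a home, so any such correlation adds to the variance of the difference between arms, and an individual-level t-test leaves that part out.

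The mismatch is notable because the trial was clustered for the sake of the staff, and the test named for this staff outcome ignores the cluster. The article names the method outright, so this is not a detail left open for a later analysis plan. What is at stake is a false claim that the intervention reduces sick days, or a p-value and confidence interval that overstate how firmly a difference is established.

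**Working it through.** **Inputs from the article.** At least 24 homes; at least m = 6 staff per home, so at least 24 × 6 = 144 staff; α = 0.05 (stated for the primary power analysis). It states no sample size, effect size or ICC for Hypothesis 4, so there is no figure to reproduce.

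**Assumptions.** Two-sided testing; 12 homes per arm; individual caregivers as the unit of analysis; ICC between 0.01 and 0.20; m = 10 as a second case, because 6 is a minimum.

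**Formulas.** Design effect DE = 1 + (m − 1) × ICC. The unadjusted test understates the standard error by a factor √DE, so its actual type I error is 2 × [1 − Φ(1.96/√DE)]. The effective sample is 24m/DE.

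**Worked case, m = 6, ICC = 0.05.** DE = 1 + 5 × 0.05 = 1.25. 1.96/√1.25 = 1.753. Type I error = 2 × [1 − Φ(1.753)] = 0.080. Effective sample = 144/1.25 = 115.

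| ICC (assumed) | DE, m = 6 | Type I error, m = 6 | Effective n of 144 | DE, m = 10 | Type I error, m = 10 |
|---|---|---|---|---|---|
| 0.01 | 1.05 | 5.6% | 137 | 1.09 | 6.1% |
| 0.02 | 1.10 | 6.2% | 131 | 1.18 | 7.1% |
| 0.05 | 1.25 | 8.0% | 115 | 1.45 | 10.4% |
| 0.10 | 1.50 | 11.0% | 96 | 1.90 | 15.5% |
| 0.20 | 2.00 | 16.6% | 72 | 2.80 | 24.2% |

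**Check by simulation** (20,000 null trials per setting, 12 homes per arm, 6 staff per home).

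- Normal data: the individual-level t-test rejects in 5.5%, 6.0%, 8.1%, 10.4% and 16.7% at ICC 0.01, 0.02, 0.05, 0.10 and 0.20, in line with the formula.
- Skewed negative binomial counts (assumed mean 10, dispersion 0.5): 5.4%, 6.2%, 6.9%, 9.4% and 12.0% at the same nominal ICCs. The lower figures at the top of the range arise because the multiplicative home effect also raises the within-home variance. At nominal 0.20 the home multiplier has variance 0.20 × 210/100 = 0.42, the total variance is 10 + 100 × [(1.42 × 3) − 1] = 336, and the realised ICC is 42/336 = 0.125. The formula then gives DE = 1.625 and 12.4%, close to the simulated 12.0%.
- t-test on home means (24 − 2 = 22 df): 4.1% to 5.0% in every setting, normal or skewed.

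**Is clustering the cause?** With skewed counts and ICC 0, the individual-level t-test rejects in 4.7%. Adding unequal observation time (0.3 to 1 of the period) gives 4.5%. At nominal ICC 0.05, skewed counts give 6.9% with equal time and 6.8% with unequal time. The excess comes from clustering.

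**The case against.** The best defence is that the article does not state the unit of analysis. An independent-samples t-test run on home means would fit the named test and would be valid. That stands as a point of wording: the individual-level reading is the natural one, since the comparison is described as being among caregivers and no averaging is mentioned, but it remains an inference.

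It is also fair to say that the size depends on an ICC the article does not give, and that at 0.01 to 0.02 with 6 staff per home the excess is only about one percentage point. This limits the size of the problem, not its direction, and 6 is a minimum.

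A reader might infer more than the article supports:

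- *That skewed counts or unequal observation time invalidate the p-value.* The article describes neither, and at about 72 staff per arm neither inflated the type I error in simulation. They bear on efficiency and on the choice of effect measure.
- *That the wording of Hypothesis 4 is itself a flaw*, because it says that the trend of Hypothesis 3 "will lead to a relevant reduction in the number of days spent unable to work for this group of individuals". This reads as a rationale. The analysis section restates the tested quantity as a difference between arms, and no mediation analysis is planned or claimed.
- *That the error distorts the economic evaluation.* That analysis concerns the same variable but is not made conditional on the t-test. With similar staff numbers per home, ignoring clustering understates the standard error without biasing the mean difference.

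**Conclusion.** The concern holds on clustering alone. On the natural reading, the test named for Hypothesis 4 ignores the unit of randomisation and exceeds its 5% level for any positive within-home correlation: slightly at ICC 0.01 (5.6%), materially from about 0.05 (8.0%), and threefold at 0.20 (16.6%), all with 6 staff per home. These figures rest on an assumed ICC range, a two-sided test, 12 homes per arm and caregivers as the unit of analysis.

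Because the outcome is secondary, the conclusion on the primary endpoints is not affected. The change should be made, but it does not call the trial's main result into question.

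**What to change.** State in the analysis section that Hypothesis 4 is tested with the nursing home as the unit. Either of two versions would do:

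1. Average the days unable to work within each home and compare the home means between arms with a t-test, on 22 df if 24 homes are analysed.
2. Fit a mixed or GEE count model with home as the cluster and a small-sample correction suited to about 24 clusters. Add an offset for observation time only if that time turns out to differ between staff.

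If home means were intended all along, one sentence saying so settles the point.

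The first version needs no new data and no new software. The cost is a change of analysis wording and a somewhat wider confidence interval for this secondary outcome. The true standard error exceeds the unadjusted one by √DE, which for 6 staff per home is a factor of 1.12 at ICC 0.05 (√1.25) and 1.41 at ICC 0.20 (√2.00).
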